## Abstract

**Background:**

Vulnerable older adults have a high risk of morbidity and mortality. Regular physical activity (PA) can have a positive effect on the health and health-related behavior of this specific target group. However, evidence of the impact and feasibility of community-based PA promotion interventions for vulnerable older adults is still limited.

**Objective:**

The BeTaSen (Bewegungs-Tandems in den Lebenswelten Chemnitzer Seniorinnen und Senioren: ein Beitrag zur kommunalen Gesundheitsförderung) study aims to evaluate the (1) impact as well as the (2) feasibility, acceptance, and usefulness of a 12-month low-threshold PA intervention program for community-dwelling vulnerable older adults.

**Methods:**

For our population-based prospective observational cohort study, a total of 120 vulnerable older adults (aged 75 years or older) in the area of Chemnitz (Germany) will be recruited to participate in (1) weekly neighborhood-based low-threshold PA meetings with trained mentors (activity tandems) and (2) monthly exercise meetings led by trained exercise instructors. Within the intervention, participants will be encouraged to perform the PA independently. Participants will complete assessments, which will include questionnaires as well as objective measurements of their physical, cognitive, and psychosocial health at 3 different time points (baseline, 6 months after the start, and 6 months after the end of the intervention). Additionally, a process evaluation will be performed, including questionnaires and qualitative interviews, involving the participants, mentors, and municipal project partner representatives.

**Results:**

The BeTaSen project process began in October 2021, with the start of data collection and intervention in August 2022 in the first neighborhoods of the city of Chemnitz. A total of 86 participants were recruited at the time of submission of the manuscript. Longitudinal results are expected by 2025.

**Conclusions:**

This study’s results will provide insights on (1) the PA behavior of vulnerable older adults as well as the impact of PA interventions on health-related outcomes such as cognitive, physical, and psychosocial health, and (2) the feasible and useful components of community-based PA interventions. Thus, this pilot study contributes to future recommendations and provides a basis for further research, such as the development of feasible and sustainable target group–specific interventions in community settings.

**International Registered Report Identifier (IRRID):**

DERR1-10.2196/51462

## Introduction

### Overview

The share of older adults in many European countries’ total population is increasing [1]. Aging is associated with a number of physical and health-related changes, including a decline in physical and cognitive performance and an increase in neurodegenerative as well as cardiovascular diseases [2]. Furthermore, demographic developments and age-related increases in individual disease risk pose significant (health-related) economic and social challenges for aging societies. This manifests itself in increased hospitalizations [3] and financial burdens on both the health care system and private households due to rising health care costs [4]. Thus, healthy aging, for example, years of life spent in good health and the maintenance of well-being in old age, has enhanced attention in social and health systems [2]; investments in and programs to promote health are increasing in importance. According to current research, vulnerability in older adults (eg, poverty, loneliness, and a low level of education) can adversely affect the health behavior, morbidity, and mortality of older adults [5-9]. German adults with an income of less than 60% of the national average, for example, have a significantly reduced life expectancy compared to those with above-average incomes [8]. Consequently, it is crucial to focus, especially on these target groups, on health promotion programs.

Among other health-promoting interventions, recent studies confirm that regular physical activity (PA), for example, daily walks, can improve individual and biopsychosocial health among healthy as well as vulnerable older adults [10-16]. Moreover, regular PA can also have a positive impact on social connectedness [13], which in turn can improve older adults’ cognitive and mental health and seems to be a relevant factor in successful aging [14]. Accordingly, regular PA can be considered a beneficial investment in individual health capital [15] and in healthy aging in general [11]. Furthermore, previous studies and systematic reviews have shown that PA interventions in community settings can improve older adults’ physical function and level of PA [16-20], even in those who are vulnerable [16,20]. For example, Giné-Garriga et al [16] find that physical exercise interventions can improve physical function in frail older adults. Other studies conclude that such programs can have positive effects on older adults’ cognitive and mental health [21,22]. Recently, studies investigated the impact of community-based PA interventions on older adults’ cognitive, psychosocial, and physical health and on their PA behavior in German communities [23,24]. However, many studies involved mostly healthy older adults who did not belong to a vulnerable group, and current research does not address long-term implications or specific group differences.

Thus, more evidence is needed to confirm these positive impacts, especially on vulnerable older adults, and to implement subsequent health promotion programs. Furthermore, despite the well-known positive effects of regular PA, only a small fraction of older adults in Germany are sufficiently physically active in line with the recommendations of the World Health Organization (WHO) [25]. The WHO and the American College of Sports Medicine recommend adults aged 65 years or older perform moderate to vigorous endurance training for a minimum of 150 minutes per week (in bouts of at least 10 minutes each) [26], in addition to flexibility, strength, and balance training twice per week [25]. Among adults aged 65 years or older, 42% meet the recommendations for endurance training, while only 29% meet those for strength training [25]. In a German health monitoring survey, 36% of older adults aged between 60 and 69 years and nearly 45% of older adults aged between 70 and 79 years reported that they do not engage in any regular PA or exercise [27]. Several studies find that vulnerability, for example, a low level of education, physical restrictions, and poor health status, is negatively associated with older adults’ PA level (eg, meeting the WHO’s recommended level of PA) [25]. This specific group is thus exposed to severe health risks and potentially early care dependency [5-8]. Due to the high share of older adults who are physically inactive, feasible PA promotion programs targeted specifically at previously physically inactive or vulnerable older adults are especially relevant. To determine the feasibility and sustainability of PA programs targeted specifically at vulnerable older adults, further research on contributing factors and barriers is needed. The literature identifies several internal and external barriers for older adults’ participation in PA programs: lack of information about PA offers, physical restrictions, lack of social support to begin with PA, lack of language skills and local accessibility, as well as financial costs [28]. Vulnerable older adults (eg, poverty, loneliness, and a low level of education) perceive high barriers to participation in health-related promotion programs, for example, PA programs [29]. In a systemic review, Franco et al [30] identified six major themes that may influence older adults’ participation in PA: (1) social influences, (2) physical restrictions, (3) competing priorities, (4) access difficulties, (5) lack of awareness of the personal benefits of PA, and (6) motivation and beliefs [30]. Furthermore, current research recommends providing PA interventions in community settings for vulnerable older adults that are specifically tailored to the target group and embedded in their immediate social-spatial context (districts and neighborhoods) [31-33]. Moreover, previous studies have shown that personal interventions are particularly effective in promoting PA [34] and that motivators such as social and environmental support, convenience of location, and enjoyment of the activity seem to be relevant factors in interventions targeted at community-dwelling older adults [35]. These influencing factors should be considered when developing exercise interventions to promote PA and its associated positive health benefits among vulnerable community-dwelling older adults.

Some studies conclude that community-based PA programs for older adults are feasible, even over a longer period [36-38]. A systematic review carried out by Farrance et al [39], for example, finds long-term adherence rates of nearly 70% for community-based group exercise programs. Nevertheless, there is limited evidence about the long-term adherence measures included in these programs as well as participants’ views [39]. Shvedko et al [40] assert that a PA intervention for community-dwelling older adults at risk of loneliness is accepted by older adults and is feasible. Crombie et al [41] also show that a community-based PA intervention is feasible for sedentary older adults. However, recent evidence about the feasibility and acceptance of community-based PA interventions and of the different components of such interventions, especially among vulnerable older adults, is limited.

In summary, evidence of the impact and feasibility of PA interventions on the health and health-related behavior of vulnerable community-dwelling older adults remains sparse. Therefore, research should focus on the health-related benefits of intervention programs that promote PA among vulnerable older adults as well as on how intervention programs tackle (internal and external) barriers that discourage the participation of vulnerable older adults in PA programs.

For this reason, the aim of this study is to investigate the impact and feasibility of a 12-month low-threshold targeted PA intervention program on community-dwelling vulnerable older adults. This study protocol describes the study’s objectives, the design of the intervention, method, data collection, and considerations for analyzing the data from the PA intervention program of the study BeTaSen (Bewegungs-Tandems in den Lebenswelten Chemnitzer Seniorinnen und Senioren: ein Beitrag zur kommunalen Gesundheitsförderung).

### Research Objectives and Research Questions

The main goal of the BeTaSen study is to initiate, sustainably maintain, and promote an active and healthy lifestyle for vulnerable older adults who reside in Chemnitz.

The objectives of the BeTaSen study are described in subsequent paragraphs.

Evaluation of the impact of a 12-month low-threshold PA intervention program on health-related outcomes of vulnerable community-dwelling older adults. In this context, the main research questions are as follows: (1) What are the long-term outcomes for older adults after completing a 12-month, target group-specific community-based PA program? Older adults’ PA behavior as well as their physical, cognitive, and psychosocial health are of particular interest in this regard. (2) Are any group differences evident in the long-term outcomes of a 12-month target group-specific community-based PA program among older adults (eg, gender, previous disease, and vulnerability)?

Analyzing the feasibility, acceptance, and usefulness of aspects of a community-based PA intervention for vulnerable community-dwelling older adults. In this context, the main research questions are as follows: (1) Which PA-promoting exercises and activities are considered useful by older adults? (2) Is a target group-specific 12-month PA program feasible for vulnerable community-dwelling older adults and the community setting? and (3) What factors promote or inhibit the successful implementation of a target group-specific PA program for vulnerable community-dwelling older adults?

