### Measures

All participants will complete an assessment at baseline (T1), at the end of the 12-month intervention (T2), and 6 months after the end of the intervention (T3). Before each assessment, participants will be asked to fill out a self-administered questionnaire and, for the detection of objective PA behavior, will be given a pedometer to wear for 7 consecutive days. The questionnaire will assess the older adults’ psychosocial and physical health and evaluate motivational aspects related to PA in a community setting. Sociodemographic information will be assessed within the questionnaire at T1 only, comprising target group-specific items from the German Health Interview and Examination Survey for Adults [49].

Further measurements will take place in communal facilities in the older adults’ neighborhood and will be carried out by qualified staff members. Each assessment will start with the measurement of anthropometric data (height and weight) as well as the registration of current medication intake and existing diagnosed diseases via interview. Using the EQ-5D-3L questionnaire, the participants’ subjectively perceived health status in terms of mobility, self-care, regular daily activities, pain, discomfort, anxiety, and depression will then be determined by interview (3 response options: no problems, some problems, and serious problems) [50]. Additionally, their general self-rated health status will be recorded using the vertical visual analog scale EQ-VAS (1-100) [50].

An additional process evaluation will be performed during the intervention period using questionnaires for participants (after a period of 4 weeks) and mentors (after the workshop, 3 months after the intervention). Furthermore, qualitative interviews and informal notes, reports, and documentation of the PA groups will also be obtained from the activity tandems as well as from group meetings (Table 1 for a summary of outcomes).

**Table 1 table1:** Outcome measurements of the population-based prospective observational cohort study BeTaSen (Bewegungs-Tandems in den Lebenswelten Chemnitzer Seniorinnen und Senioren: ein Beitrag zur kommunalen Gesundheitsförderung). T1 is baseline, T2 is the end of the intervention period (12 months), and T3 is 6 months after the end of the intervention (study population: older adults aged 75 years or older living in Chemnitz, Germany).

Assessment		Instrument or scale	Time of measurement	
**Outcome**				T1, T2, T3

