### Statistical Analysis

SPSS Statistics (version 29; IBM Corp) and AMOS (version 29; IBM Corp) will be used for all quantitative statistical analyses. To determine the primary outcome at baseline (T1), the study population will be descriptively characterized using the following outcomes: demographics (eg, age, gender, family status, and income), anthropometric comorbidities, PA and health-related behavior (eg, smoking status and alcohol consumption), as well as physical, functional, cognitive, and psychosocial health status. Furthermore, participants’ data at the end of the intervention period (T2) and 6 months after its end (T3) will be analyzed to evaluate the long-term impacts, feasibility, and usefulness of the PA intervention. Time effects, group differences (eg, age, gender, vulnerability, and sociodemographic conditions) in terms of physical, cognitive, and psychosocial health, interaction effects, as well as the intervention’s feasibility and sustainability, will be analyzed using different parametric or nonparametric statistical methods such as the *t* test, Mann-Whitney *U* test, ANOVA, or Kruskal-Wallis test, depending on the number and size of the group, normal distribution, and homoscedasticity of the sample. Based on current evidence [6-8,25], associations and the strength of the relationship between 2 variables (eg, PA behavior and monthly income and adherence rate and level of education), correlation and regression analyses as well as adjustments for relevant covariates (eg, age, gender, and vulnerable criterion) will be performed. Additionally, multilevel analyses are planned to estimate, for example, the within-person impacts of the intervention program (eg, the impact of PA on well-being).

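### Time effects are assigned to tests that, in their usual paired or repeated-measures form, drop people with a missing visit; the mixed model already planned should be the main analysis

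*Protocol article*

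**What the plan says.** All of the following is in the protocol article.

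- **Objective** (Research Objectives and Research Questions): "Evaluation of the impact of a 12-month low-threshold PA intervention program on health-related outcomes of vulnerable community-dwelling older adults". It carries no condition that the program be finished.
- **Research question 1** (same section): "What are the long-term outcomes for older adults after completing a 12-month, target group-specific community-based PA program".
- **Schedule** (Measures): "All participants will complete an assessment at baseline (T1), at the end of the 12-month intervention (T2), and 6 months after the end".
- **Analysis of time effects** (Statistical Analysis): time effects, group differences, interactions and feasibility are to be analysed by "different parametric or nonparametric statistical methods such as the *t* test, Mann-Whitney *U* test, ANOVA, or Kruskal-Wallis test", the choice depending on group number and size, normality and homoscedasticity.
- **Further method** (same section): "multilevel analyses are planned to estimate, for example, the within-person impacts of the intervention program". It is introduced as an addition, and its example is the effect of activity on well-being. No sentence assigns it to the change across T1, T2 and T3.
- **Design** (Discussion): the study is not randomized or controlled.

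**The concern.** Without a comparison group, the change from T1 to T2 and T3 is the entire evidence on impact. Follow-up lasts 18 months in vulnerable people aged 75 or older, and mentor support is withdrawn step by step until the groups are essentially independent from month 10. Some missing T2 and T3 visits are to be expected, and they need not be a random sample.

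If the main time-effect analysis is a paired t test or a listwise repeated-measures ANOVA, people without the needed visit leave the estimate. The result then tells how those who stayed fared, whereas the objective asks what the program does for vulnerable older adults. The wording of question 1 can be read as accepting that narrower group, although the schedule does not.

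**Working it through.** **1. What each named test does with a missing visit**

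- Paired t test, T1 against T2: drops people without T2 and keeps those who miss only T3.
- Paired t test, T1 against T3: drops people without T3.
- Repeated-measures ANOVA over three visits with listwise deletion: drops anyone missing T2 or T3.
- Mann-Whitney U and Kruskal-Wallis: tests for independent groups. Applied across visits, they would ignore the pairing and compare whoever happens to be present.
- Linear mixed model fitted by maximum likelihood: uses every visit that was made.

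**2. Inputs for the size**

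- Target number: about 120 (Design and Organization of a Physical Activity–Promoting Intervention). It is set by feasibility, so there is no power calculation to reproduce. Consistency check: 4 districts × 24 to 32 people = 96 to 128, which contains 120.
- Retention: not given. Assumed loss *q* = 10%, 20% or 30%.
- Difference in mean change between those who stay and those lost: not given. Assumed *d* = 0.2 to 0.5, in units of the SD of change.

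**3. Shift of the complete-case mean**

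Mean of all = (1 − *q*) × mean of stayers + *q* × mean of those lost. Hence stayers − all = *q* × *d*. The standard error of the complete-case mean is 1/√(120(1 − *q*)).

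| *q* | n left | SE | shift, *d* = 0.2 | shift, *d* = 0.5 |
|---|---|---|---|---|
| 10% | 108 | 0.096 | 0.02 SD (0.21 SE) | 0.05 SD (0.52 SE) |
| 20% | 96 | 0.102 | 0.04 SD (0.39 SE) | 0.10 SD (0.98 SE) |
| 30% | 84 | 0.109 | 0.06 SD (0.55 SE) | 0.15 SD (1.37 SE) |

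The sign follows that of *d*. If those lost would have done worse, the complete-case mean is too favourable; if better, too unfavourable.

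**4. Does the mixed model help?**

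Two simulations with n = 120 and three visits made the chance of leaving higher after a low earlier score. This is missing at random.

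- *No true change.* Visit correlation was 0.5 or 0.7, log-odds slope 0.5 or 1.0 per SD, and 29% to 33% were out by T3. Bias of the complete-case T1-to-T3 change was −0.036 and −0.082 SD (correlation 0.5) and −0.023 and −0.047 SD (correlation 0.7). Maximum likelihood on all visits gave 0.002, −0.006, 0.000 and −0.002. A repeat of this simulation agreed with every bias to within 0.01 SD.
- *True T1-to-T3 change 0.10*, about 28% lost. Complete cases gave about 0.03 and a random-intercept mixed model about 0.10. The plain mean of those seen at T3 was 0.27 against a true T1 mean of 0, so an unpaired comparison would have shown about 0.27.

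In these runs the paired complete-case change is too low, because people kept for their high earlier scores regress toward the mean. The unpaired comparison is too high. The direction therefore depends on the form of the test as well as on why people leave.

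**5. Limit of the remedy**

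The mixed model removes the part of the shift that earlier visits predict. Where loss depends on the unseen change itself, some of the *q* × *d* in step 3 remains.

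**The case against.** The strongest reply is that the article never restricts the analysis to completers. The phrase about completing the program reads naturally as a time point, after the 12 months, and then agrees with the schedule. The list of tests is open and covers more than time effects. It does not mention pairing or listwise deletion. Multilevel analysis of within-person impact is planned in the same section. Analysis sets and missing-data rules are commonly left to a fuller document.

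Most of this stands. It rules out several stronger readings that a reader might infer:

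- *That the long-term result is fixed as a completer result.* It is not; it may become one, depending on which test is used.
- *That leaving the tandems means leaving the analysis.* Under the schedule, someone who stops attending is still due at T2 and T3, and any of the tests would count that person if assessed.
- *That about 30% will not complete.* The Overview says that a systematic review "finds long-term adherence rates of nearly 70% for community-based group exercise programs". Those are other programs, and this study defines adherence by sessions completed. An average of 70% of sessions is compatible with full retention.
- *That the lack of a missing-data rule is itself a fault.* In a condensed article it is not.

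What the reply does not remove is the ordering. The methods the article names for time effects are the simple tests. The model that can use every visit is an extra, and its one example is a different question.

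**Conclusion.** The point holds as a recommendation about method. For an uncontrolled study of this population, the tests named for time effects are a weaker choice than the multilevel model already in the plan, since their usual within-person forms discard people with a missing visit. On the assumptions above (10% to 30% of 120 lost, mean change differing by 0.2 to 0.5 SD), the complete-case mean is off by 0.02 to 0.15 SD, about 0.2 to 1.4 standard errors, in a direction that cannot be fixed in advance. With little loss, or loss unrelated to outcome, the effect is negligible. The wording of question 1 is an ambiguity worth removing. It is not a proven contradiction with the schedule.

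**What to change.** - **Statistical Analysis:** name the planned multilevel (linear mixed) model as the main analysis of time effects. Take T1, T2 and T3 as a fixed categorical time factor, and fit by maximum likelihood to every available visit of all participants with a T1 assessment. Report complete-case or completer results as secondary, with completion defined from the attendance records.
- **Research question 1:** word it for everyone who starts the program, in line with the objective and the schedule.
- **Conduct:** keep inviting people who stop attending the tandems to the T2 and T3 assessments, as the schedule already implies.

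The cost is a few sentences and some follow-up calls or letters. No new measurement, participants or software are needed. The headline change may look less favourable than among those who stayed, and the model's validity rests on data being missing at random, which should be stated with the result.
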